#### Enrollment survey:

The enrollment survey will be used to enroll participants after they provided consent. It contains questions on demographic details of the participant including age, sex, school enrollment, occupation, study site, as well as household characteristics such as household size and composition, and sources of water.

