#### Electronic proximity sensor study

*Sample size*: We will recruit 63 households per site (126 per country). At each site, households with a child aged <6 months, 6–11 months, 1–4-years were selected randomly and proportional to these age groups.

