##### Study procedures:

To train all the participants in diary-keeping and sensor-wearing procedures, we will request the head of the household to select a day of the week when all household members will be present at the same time. On this selected day (start day), we will visit the household and train the members on the diary and sensor study procedures (figures 3 and 4). Each participant will wear the sensor over 7 continuous days for data collection. Participants will be required to doff the sensor when not in use such as when sleeping or leaving the house, or when encountering water. In addition, the head of the household will select one day at random (diary day one) between the start day and end day (7 days after start day). Each household member will be required to keep a record of their contacts in the paper diary on two consecutive days. The research team will record the date and time when the sensors were issued and collected, while participants will keep a daily log of when the sensors were worn or taken off. Data from each sensor will be individually downloaded into a laptop at the site office.

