##### Validation of diary-based collection (Sensor Study).

We will use the sensor data to validate the diary data using two methods. First, using variables that characterize each contact such as age, sex, duration, and relationship, we will identify contacts that were identified by [1] diary, [2] sensor, or [3] both. We will then calculate the level of agreement between diary and sensor data using Cohen’s kappa coefficient (k). Second, using sensor data, we will construct age-specific contact matrices containing the average number of contacts made per day using the methods described in the contact diary study. We will compare these matrices with those generated from diary data but restricted to household contacts using the coefficient of accuracy (C(a) and the coefficient of determination (r_c_). C(a) measures the accuracy and r_c_ measures the precision of the relationship between the two data collection methods (32). We will then perform the same comparisons for data on the duration of contacts.

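### The precision coefficient r_c in the matrix-level diary validation has a high floor set by household composition, so it does not by itself show that diary and sensor agree

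*Protocol article*

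**What the plan says.** The section *Validation of diary-based collection (Sensor Study)* plans two methods.

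- **Contact level.** Contacts are classed as found by diary, by sensor or by both: "We will then calculate the level of agreement between diary and sensor data using" Cohen's kappa.
- **Matrix level.** Sensor data are turned into age-specific matrices "containing the average number of contacts made per day using the methods described in the contact diary study". Then: "We will compare these matrices with those generated from diary data but restricted to household contacts using the coefficient of accuracy" and a second coefficient, r_c. The stated reading is that "C(a) measures the accuracy and r_c_ measures the precision of the relationship between the two data collection methods". The comparisons are repeated for duration.

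On the source of the data, *Electronic proximity sensor study* says "We will recruit 63 households per site (126 per country"). These are households with a child under 5 that "were selected randomly and proportional to these age groups". *Study procedures* says "Each participant will wear the sensor over 7 continuous days for data collection", and has every household member keep a diary on two consecutive days. The Discussion notes that sensors register only other sensor wearers. The enrollment survey collects "household characteristics such as household size and composition".

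The article gives no adjustment of the matrices for household composition and no reference value for r_c.

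**The concern.** Once contacts are restricted to the household, a cell is the product of two things: how many co-residents of age j a participant of age i has, and how often the tool records a contact with each of them. The first factor is a property of the household, not an output of either tool, and it is the same in both matrices if the same households supply both. In households selected for having a young child it can differ strongly between cells. A correlation across cells then largely reproduces who lives with whom.

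At stake is the interpretation. A high r_c would be reported as precision of the diary against the sensor when much of it could arise with no agreement on which people were in contact. It could also be carried over to contacts outside the home. The primary diary matrices include those contacts, and no shared roster supports agreement there.

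**Working it through.** The article states no value for C(a), r_c or kappa, so there is no figure to reproduce.

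**Inputs from the protocol article:** 63 households per site, 10 age groups, 7 sensor days, 2 diary days, cells in average contacts per day.

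**Assumed, because the article does not give them:** mean household size 4.5, 6 or 8, with an age composition; recording probability 0.3 to 0.9 per pair and tool; each pair counted at most once a day; diary and sensor records independent given co-residence, so that true kappa is 0.

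**Structure.** Let A_ij = (ordered co-resident pairs of ages i, j) / (participants of age i). Then

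- sensor cell = A_ij × s_ij
- diary cell = A_ij × d_ij

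If s and d do not vary by age pair, both matrices are proportional to A. Apart from sampling noise r is then 1, whatever the agreement on individual pairs.

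**C(a) behaves differently.** C(a) = 2·s_x·s_y / [s_x² + s_y² + (m_x − m_y)²], with m and s the mean and SD over cells. If diary = k × sensor, this becomes 2k / [1 + k² + (1 − k)²(m/s)²]. Taking m/s = 1 for illustration:

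- k = 1: 2/2 = 1.00
- k = 0.5/0.9 = 0.556: 1.111 / (1 + 0.309 + 0.198) = 0.74
- k = 0.3/0.9 = 0.333: 0.667 / (1 + 0.111 + 0.444) = 0.43

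So C(a) tracks the gap in overall level, not the roster.

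**Simulation, one site, rates uniform across age pairs** (ranges over the three household sizes; 40 replicates per scenario):

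| Scenario | r | C(a) |
|---|---|---|
| Equal rates, records redrawn daily | 0.86-0.99 | 0.99-1.00 |
| Equal rates, pair status fixed over days | 0.67-0.99 | 0.98-1.00 |
| Rates 0.9 v 0.7 | 0.94-0.98 | 0.91-0.95 |
| Rates 0.9 v 0.5, either direction | 0.89-0.99 | 0.64-0.76 |
| Rates 0.9 v 0.3, either direction | 0.79-0.97 | 0.33-0.49 |
| Diary records exactly the pairs the sensor misses, rate 0.5 | 0.62-0.73 | 0.99 |
| Independent durations, equal rates | 0.58-0.95 | 0.98-1.00 |

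Kappa was between -0.014 and 0.013 in every independent scenario and about -1 in the row of exact opposites. A separate run of 400 simulated studies per scenario (about 6 members per household, rates 0.5 to 0.9, redrawn daily) gave median r of 0.95-0.98.

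**Isolating the cause.** With each cell divided by its number of available pairs, r in the independent scenarios fell to between -0.09 and 0.08. The roster produces the correlation.

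**Relaxing uniform rates.** With each tool's rates varying independently by age pair on the logit scale, median r was 0.86, 0.68 and 0.54 at SD 0.5, 1.0 and 1.5. A second set of runs at rates 0.6/0.6 gave 0.88, 0.73 and 0.62.

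**If r_c means r squared.** The article calls r_c a coefficient of determination. Squared, 0.95-0.98 becomes 0.90-0.96, and 0.54-0.86 becomes 0.29-0.74.

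**The case against.** Several points on the other side stand.

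- **C(a).** A reader might infer that the shared roster raises both coefficients. It does not. Differing overall levels are plausible, because diary and sensor define contact differently and sensors come off for sleep and outside the house. If the sensor count is of contact episodes rather than distinct persons, which the article leaves open, C(a) fell to about 0.03-0.04 in simulation (one run assumed 15 episodes per pair per day).
- **Kappa.** A reader might infer that the whole validation cannot tell a good diary from an unrelated one. The same section plans kappa, which would be about 0 for an unrelated diary. Two limits remain. Kappa needs the pairs that neither tool recorded, which the three listed categories do not name and the roster would have to supply. It also applies to minutes only after categorisation.
- **Sensitivity of r.** Uniform recording rates are an assumption. When the tools differ by age pair r does fall, so the comparison is not blind to all disagreement.
- **The target is legitimate.** Models use average contacts by age group, availability included. Whether two tools give the same household matrix is a fair question, and per-pair rates answer a different one.
- **Shared households are inferred.** The validation section does not say outright that its diary matrices come only from sensor households. Its heading and *Study procedures* make that the natural reading.

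None of this makes the undivided r_c a measure of precision between the methods, which is the meaning the article assigns to it.

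**Conclusion.** The point holds for r_c, and as a cheap improvement rather than a fault that defeats the validation. With no pair-level agreement, r_c was about 0.95-0.98 under uniform recording rates of 0.5 to 0.9. It was lower, down to 0.67, at low rates with pair status fixed over days, and about 0.54-0.86 when the tools' rates varied independently by age pair. The duration comparison has the same weakness.

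The sizes rest on assumed household composition and recording rates, on counting each pair at most once a day (the episode run apart), and on both matrices coming from the same households. A high floor appeared at every household size tried. The documents do not support saying that C(a) is inflated, that r_c must be near 1, or that the planned validation as a whole would miss an unrelated diary.

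**What to change.** In *Validation of diary-based collection (Sensor Study)*, keep the planned matrix comparison, described as a check on whether the two tools give the same household matrix. Beside it report:

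1. C(a) and r_c on rates per available pair: each cell's contacts divided by the number of enrolled co-resident pairs of those ages, with sparse cells merged and intervals from a bootstrap of households.
2. The r_c obtained when diary entries are permuted among co-residents within each household, as the no-agreement reference.

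Do the same for duration. Base statements about diary validity on kappa and these adjusted figures, not on the undivided r_c.

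The cost is wording and analysis code. Household composition is already collected, and linking diary entries to household members is work the contact-level method needs anyway. The downside is that the agreement figures will look less favourable and some age-pair cells must be merged.

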##### Characterizing the social contact of young infants.

We will generate a detailed characterization of the social contacts of infants aged <6 months with their household members. To do this, we will calculate the infant proximity score for each household member, which is defined as the fraction of time spent by each household member in proximity with the infant, over the total infant contact time.(33) Certain demographic and behavior characteristics (e.g., maternal age, sex, household size, and country) are predictors of the infant proximity score. To evaluate the association between social contacts and these predictors, we will use regression methods such as negative binomial regression where the dependent variable is the infant proximity score.

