##### Estimating effects on total number and duration of contacts.

We hypothesize that certain demographic and behavior characteristics (e.g., maternal age, sex, household size, and country) are predictors of the frequency and nature of social contacts of young infants. Identifying these factors will aid in generalizing our findings and serve as a guide for other researchers to select the right contact matrices and determine what predictors are important to include in future analyses. To evaluate the association between predictors and the total number or duration of contacts, we will use similar regression methods as above. In addition to providing an analytical understanding of the determinants of contact frequency and types, the results from this analysis will help to guide researchers on which contact matrix is best suited to a given modeling application or generalizable to similar populations.

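### The infant proximity score is a share between 0 and 1, so negative binomial regression does not fit it; if the shares sum to 1, pooled effects of maternal age or country are uninformative

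*Protocol article*

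**What the plan says.** All of this is in the Protocol article, mostly in *Characterizing the social contact of young infants*.

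- **Unit:** "we will calculate the infant proximity score for each household member", so there is one value per member.
- **Definition:** "the fraction of time spent by each household member in proximity with the infant, over the total infant contact time". The text does not say whether the denominator adds up the members' times or counts the time with at least one member nearby.
- **Predictors:** "Certain demographic and behavior characteristics (e.g., maternal age, sex, household size, and country) are predictors of the infant proximity score".
- **Model:** "we will use regression methods such as negative binomial regression where the dependent variable is the infant proximity score". This is the only method named.

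The next section, *Estimating effects on total number and duration of contacts*, treats contact volume separately: "To evaluate the association between predictors and the total number or duration of contacts, we will use similar regression methods as above". On numbers, *Electronic proximity sensor study* says "We will recruit 63 households per site (126 per country"), which is 63 × 8 = 504 over the eight sites.

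**The concern.** A fraction is given to a model for counts. The example predictors also include three that take one value per household: maternal age, household size and country. If members' shares add up to a fixed total, such a predictor cannot move the household's average share; it can only change how the total is divided among members. A pooled analysis would then report a null for maternal age or country and an inverse effect of household size, both produced by the definition of the score. The article wants its identified predictors to guide other researchers in choosing contact matrices, so an artefact read as a finding could mislead them.

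**Working it through.** The plan states no power, alpha or effect size for this regression, so there is no figure to reproduce.

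**Step 1. Distribution (either denominator).** Negative binomial variance is μ + αμ² with α ≥ 0, so it is at least μ. A variable confined to 0–1 with mean μ has variance at most μ(1−μ), which is below μ. At μ = 0.25 the model implies at least 0.25, while a share can reach at most 0.25 × 0.75 = 0.1875. In simulated shares that sum to 1, Pearson dispersion was 0.09 for a negative binomial with α = 1 and 0.11 for Poisson (1 would indicate fit). When α was estimated by maximum likelihood it fell to about 0.

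**Step 2. Denominator = sum over members.** With member times t₁…tₘ, the score is sᵢ = tᵢ / Σt. Then Σsᵢ = 1 and the household mean is 1/m: 0.5000 at m = 2, 0.2500 at m = 4, 0.1250 at m = 8. Since log(1/m) = −log m, a log-link main-effects fit on log m and a household-constant predictor X gives −1 for log m and 0 for X. This is algebra and does not depend on the sample size.

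**Step 3. Simulation.** Assumptions, none from the documents except the 504: 504 households; 2–8 members besides the infant; binary X independent of size; mother's mean time 3 times that of any other member; 200 runs; negative binomial with log link and α = 1; household-clustered standard errors. Rows marked † are single fits on 20,000 households.

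| Shares sum to 1 | Result |
|---|---|
| X raises all contact time by 50%, pooled score model | log m: −1.000; X: 0.000 |
| Same, adding member sex or using linear household size† | X within about 0.002 of 0 |
| Same, pooled fractional logit on log m and X† | X: 0.001 |
| X raises only the mother's time by 50%, pooled score model | log m: −1.000; X: 0.000 |
| Same, mother × X term | 0.32, detected in 100% of runs |
| Same, mothers only | 0.17, detected in 99.5% of runs |
| X raises all contact time by 50%, gamma log-link model of contact time | 0.41 (log 1.5 = 0.405), detected in 100% of runs |

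Rejection rates for the pooled X coefficient are not reported, because its clustered standard error is numerically zero.

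**Step 4. Denominator = time with at least one member.** Contacts now overlap, and scores summed to about 1.4–1.5 per household. The log m slope was −0.66 with no effect of X and −0.60 when X raised contact time by 50%. In that second case X had a coefficient of 0.15, detected in 100% of runs.

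The pooled fractional logit row shows that changing the distribution alone does not cure the second problem. The mother × X and mothers-only rows show that bringing in the member's relationship to the infant does.

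**The case against.** The strongest reply is that the article fixes very little. It offers negative binomial as an example, lists predictors as examples, and does not say that members are pooled, that only main effects are fitted, or that relationship is left out. Relationship is collected, and the example household network is coloured by relationship to the infant. Clustering and covariate form are commonly left to an analysis plan. All of this stands, and it rules out several stronger readings:

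- *The model cannot detect any household-level predictor.* This holds only for pooled main effects with shares that sum to 1. A relationship interaction or a mothers-only fit detects an effect on the mother's share, and under the other denominator even the pooled model detects an effect.
- *The negative binomial causes the null.* It does not; pooling a compositional outcome does.
- *Members' scores are treated as independent.* The article states no covariance structure.
- *Household-level effects are lost to the study.* Contact number and duration are modelled separately on the same example predictors.

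Two further limits apply. The exact 1/m needs m to be the members wearing sensors, which may differ from surveyed household size. And 504 may be too many: the sensor sample is drawn from households with children in three age bands up to 4 years, while this analysis concerns infants under 6 months.

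The open phrasing does not remove the mismatch. The one method named is a count model, and the dependent variable is explicitly the fraction.

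**Conclusion.** The mismatch between a 0–1 share and a count model is established and does not depend on the denominator. The uninformative result for maternal age and country, with a slope of −1 on log m, is exact under two conditions that the article neither states nor excludes: the denominator is the sum over members, and the fit is a pooled log-link main-effects model on log m. With other links or a linear size term the household-constant coefficient is close to zero (within about 0.002 in the fits run). With an at-least-one-member denominator, the mechanical part is reduced to a slope of roughly −0.60 to −0.66 under the simulation's assumptions.

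A reader might infer that the infant analysis as a whole fails; the documents do not support that. One regression is affected. Calculating and describing the scores, the contact matrices and the separate analysis of contact volume are not. It should be corrected before the analysis is run.

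**What to change.** 1. State the denominator of the score, and whether members are counted as sensor wearers or as surveyed household members.
2. Replace negative binomial for the score. If shares sum to 1, use fractional multinomial or Dirichlet regression; otherwise use a fractional logit per member.
3. Include relationship to the infant and its interactions with maternal age, household size and country, with household-clustered standard errors.
4. Take household-level effects on contact volume from the analysis of total number and duration: negative binomial for the number of contacts, a gamma or log-linear model for duration.

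The cost is wording and code, with no new data. The downside is slightly more analysis work and more coefficients to report.

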##### Estimating effects on total number and duration of contacts.

We hypothesize that certain demographic and behavior characteristics (e.g., maternal age, sex, household size, and country) are predictors of the frequency and nature of social contacts of young infants. Identifying these factors will aid in generalizing our findings and serve as a guide for other researchers to select the right contact matrices and determine what predictors are important to include in future analyses. To evaluate the association between predictors and the total number or duration of contacts, we will use similar regression methods as above. In addition to providing an analytical understanding of the determinants of contact frequency and types, the results from this analysis will help to guide researchers on which contact matrix is best suited to a given modeling application or generalizable to similar populations.

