#### Quantitative data analysis

##### Construction of age-specific contact matrices.

The primary outcome from this analysis will be age-specific contact matrices containing the average (or expected) number of contacts made per day between age groups combinations. We will create three age-specific contact matrices for each study site: a matrix of physical contacts only, a matrix of nonphysical contacts, and a matrix of all contacts (both physical and nonphysical contacts).

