##### Identifying predictors of number and duration of contacts.

We will investigate whether certain demographic and biologic characteristics are predictors of the frequency and nature of contacts. This regression analysis will result in the identification of key drivers of contact.

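### The regression offered as a guide to choosing or transferring contact matrices models only the total number or duration of young infants' contacts, which cannot show whether age mixing agrees between populations

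*Protocol article*

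**What the plan says.** The section on estimating effects on total number and duration of contacts contains three elements.

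- **Hypothesis.** Characteristics such as maternal age, sex, household size and country are expected to be "predictors of the frequency and nature of social contacts of young infants".
- **Model.** "To evaluate the association between predictors and the total number or duration of contacts, we will use similar regression methods as above". The methods referred to are those of the preceding section, which names negative binomial regression as an example.
- **Use.** The results are meant to "guide researchers on which contact matrix is best suited to a given modeling application or generalizable to similar populations".

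The section on constructing the matrices makes the primary outcome "age-specific contact matrices containing the average (or expected) number of contacts made per day between age groups combinations", produced for each site in three versions (physical, nonphysical, all). The Contact diary section lists ten age groups for contacts, and the sample size section uses the same ten for participants.

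**The concern.** The outcome that is modelled and the conclusion drawn from it are different quantities. Choosing a matrix for another population depends on who meets whom by age. A total adds that information away. A predictor that moves infants' contacts from school-age siblings to grandparents, with the total unchanged, has a true coefficient of zero in this model even though the infant row of the matrix has changed.

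The section's hypothesis mentions both frequency and nature of contacts, but the outcome it names keeps only number and duration. The hypothesis is also confined to young infants, whereas the advice concerns whole matrices.

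At stake is the study's guidance to modellers. Country, setting or household size could appear unimportant for matrix choice because they do not shift infants' totals, while the mixing pattern does depend on them. The Introduction criticises earlier work because differences between populations could not be interpreted. A standardised multi-country study should be able to do better than that.

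**Working it through.** The plan gives no figure on this point, and no alpha, margin or decision rule, so there is nothing to reproduce. The check is one of logic, followed by two illustrations with assumed inputs.

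**1. What a total identifies.** Write the mean daily contacts of participant age group i with contact age group j as c_ij = T_i × p_ij, where T_i is the row total and p_ij the share of contacts in age group j. Between sites A and B:

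log(c_ij,A / c_ij,B) = log(T_i,A / T_i,B) + log(p_ij,A / p_ij,B)

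The planned regression addresses only the first term, and only for the infant row. With ten age groups the matrix has 10 × 10 = 100 cells. The infant row has 10 cells, whose total fixes one sum and leaves nine quantities free. The other 90 cells belong to rows outside the hypothesis. If the section uses sensor data (it does not say which source), the total covers even less than the row, because the Discussion notes that only contacts between people wearing sensors are recorded.

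**2. Whole-matrix illustration (all inputs assumed).** Three groups (child, adult, elder) with population shares 0.40/0.50/0.10 and totals of 14/10/6 contacts per day. Mixing is C = (1 − e) × proportionate + e × diagonal, which keeps contacts reciprocal. The proportionate child-child cell is 14 × (0.40 × 14) / 11.2 = 7.00, where 11.2 = 0.40 × 14 + 0.50 × 10 + 0.10 × 6. At e = 0.75 it is 0.25 × 7.00 + 0.75 × 14 = 12.25.

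| e | Row totals | Child-child | Child-adult | Dominant eigenvalue | Share of infections in children |
|---|---|---|---|---|---|
| 0 | 14/10/6 | 7.00 | 6.25 | 11.79 | 0.50 |
| 0.25 | 14/10/6 | 8.75 | 4.69 | 11.94 | 0.53 |
| 0.50 | 14/10/6 | 10.50 | 3.12 | 12.20 | 0.59 |
| 0.75 | 14/10/6 | 12.25 | 1.56 | 12.75 | 0.71 |

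A regression on totals cannot tell these four matrices apart.

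**3. Infant-row illustration (all inputs assumed).** Two sites with 8 contacts per infant per day, split between two contact-age bands whose members are infectious with probability 0.04 and 0.01.

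- Split 6 + 2: 6 × 0.04 + 2 × 0.01 = 0.26. Split 2 + 6: 2 × 0.04 + 6 × 0.01 = 0.14. Ratio 1.86.
- Milder split, 5 + 3 against 3 + 5: 0.23 against 0.17. Ratio 1.35.
- Probabilities 0.02 and 0.01 with the first split: 0.14 against 0.10. Ratio 1.40.

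The ratio depends on the assumptions. In every case the totals are equal.

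**4. Whether another stated analysis fills the gap.**

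- The section on predictors of number and duration says "We will investigate whether certain demographic and biologic characteristics are predictors of the frequency and nature of contacts". It names no outcome by age of contact, and its heading is again number and duration.
- The validation section says "We will compare these matrices with those generated from diary data but restricted to household contacts". That sets sensor against diary, not site against site.
- The section characterising young infants' contacts fits a regression "where the dependent variable is the infant proximity score". This describes how an infant's contact time is shared within the household, but it is not an age-by-age matrix and is not linked to matrix choice.
- The network section gives descriptive household statistics.

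None of these compares age mixing between sites.

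**The case against.** The strongest reply is that the plan makes no decision on this basis. It says only that the results will help to guide researchers. A reader might infer that populations with equal totals will be declared alike. The text does not support that: it contains no equivalence test, margin or rule by which a null coefficient makes a matrix transferable. Different mixing would go unnoticed by this model, which is a weaker statement. In addition, the site-specific matrices and underlying data are to be made public, so a modeller can see the age-by-age cells directly. Both points stand and limit the consequence.

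A reader might also infer that a country effect on the total would mislead because only the scale differs. That does not hold. The cells are mean counts per day, so a difference in scale is a real difference between matrices.

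It can also be said that the model is blind only to shifts that offset each other, and that nothing in the document shows such shifts to be likely. This is fair as regards size. Simulations that set totals equal and then find the test on totals rejecting at about its alpha show only what was built in. The power of an age-of-contact test in such simulations depends on assumed means, dispersion, age split and clustering, so it is not a property of this study.

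Finally, model detail is commonly left to the full plan. That does not answer the point: the article itself states both the outcome and the inference, and the second does not follow from the first.

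**Conclusion.** The concern holds in a limited form. The section promises guidance on matrix choice and generalisability from a regression whose outcome is at most the sum of the infant row. A difference in totals shows that matrices differ, but agreement in totals does not show that they agree. The other nine participant age groups are outside the hypothesis, and no stated analysis compares age mixing between sites.

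This conclusion rests on the article's wording and on simple algebra, with no distributional assumption. How far mixing differs across these sites at similar totals is unknown, so no error rate or power figure can be given for this study. The illustrations show only that the difference can be material. The primary outcome, the data collection and the published matrices are unaffected. What is at risk is the guidance attached to this regression, which should be corrected.

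**What to change.** 1. Keep the regression on total number and duration, but limit its conclusion to infants' contact volume and duration. Remove matrix choice and generalisability from what it is said to inform.
2. Base any statement on matrix choice or generalisability on the diary data for all ten participant age groups, by one or both of:
   - a count model with contacts by age group of the contact as the outcome and a predictor × contact-age-group interaction, allowing for clustering within participant (two diary days) and household;
   - a direct comparison of site matrices, with intervals from a participant- or household-level bootstrap.
3. Say that a lack of difference in totals is not evidence that a matrix transfers.

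The cost is analysis wording and code, since the diary already records the contact's age. The downside is more parameters, so sparse contact-age groups may need to be merged. If the added analysis is not wanted, the first step alone removes the mismatch, but the study then offers no formal basis for advice on transferring matrices.
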